#### Sampling methods

The original design included a targeted enrollment of 300 practices, but was revised to reflect a target of 250 practices early in the implementation phase to address feasibility concerns. According to the design, the practices are nested within counties, which are nested within 5 geographic sectors (4 quadrants of the state plus 2 metropolitan areas of Oklahoma and Tulsa counties). A total of 50 practices were sampled per quadrant and 25 practices were sampled per metro area (Fig. 2). The quadrant area boundaries were based on the Area Health Education Centers (AHEC) boundaries [37]. When developing the sampling scheme, a convenience sample of practices was drawn from within each county with the exception of counties that share a CHIO. Counties that share a CHIO were considered a single sampling unit; therefore, practices were sampled from each of the 75 counties or paired county units. At the completion of recruitment in November 2015, a total of 263 practices consented and were recruited (Fig. 4).

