The effect of the implementation support strategy on the mean capacity to change score (priority for improvement, change capacity, and care process content), or the log odds of dichotomous indicators of change, will be estimated using GEE to fit linear and logistic regression models, respectively, based on a within-cluster and between-cluster analysis [42]. As discussed by Hussey and Hughes [42], GEE has several attractive properties that are relevant to the analysis of data arising from stepped wedge designs, including accommodating generalized linear models that are appropriate for continuous, count and dichotomous outcome measures, as well as robustness to variance and covariance misspecification. The small sample limitations of GEE-based estimation will not be of concern in this study given that 263 practices will serve as the unit of randomization and 11 time points will be utilized in the design. The outcome variable will be a continuous score measure or a Yes/No indicator variable measures at a practice unit level. The exposure of interest will be a dummy variable indicating the implementation support strategy exposure, which will be coded according to the randomized assignment (intent-to-treat analysis). Practice unit-level data will be analyzed where the nested clustering of practice units nested within practices, nested within sub-regions will be accounted for using a structured working correlation structure [44]. Cluster sizes, by county, will vary due to the targeted sampling of metro counties (25 practices per county) and more rural counties (one to five practices per county) and therefore, a jackknife estimate of the variance will be used to maintain the size of the test [42]. The time since the initiation of the implementation support strategy will also be considered as an independent factor in the regression model, along with a time by implementation support strategy interaction, to investigate the effect of the implementation support strategy relative to the time since initiation (i.e., delayed treatment effect). If a significant time by implementation support strategy effect is found, the analyses will be stratified by time period to estimate the time-specific implementation support strategy effect. Time-varying secular trends will be considered in the model, including the implementation of other health intervention programs in the studied sub-regions. Geographic region will also be considered as a modifying factor where region is fit as a series of four indicator variables (indicator for each quadrant, with the combined Tulsa and Oklahoma City metro areas serving as the reference group). If appropriate based on estimates, a dichotomous region variable indicating metro versus non-metro locations will be considered. A Type III Wald statistic will be used to determine the overall significance of the interaction between implementation support strategy and the five degrees of freedom categorical class variable for region. A 2-sided 0.05 alpha level will be used to define statistical significance. An intention-to-treat paradigm will be followed where data from all practice units are analyzed according to the randomized assignment regardless of adherence or implementation quality.

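### The jackknife is said to keep the 0.05 size, but the metro level of the region-by-support test is only two counties; deleting counties with a large-sample Wald reference, that test rejects a true null about 11-18% of the time

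*Protocol article*

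**What the plan says.** All of this is in the protocol article, Methods, Evaluation.

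- **Analytic plan, variance.** County is the cluster whose unequal size prompts the jackknife: "Cluster sizes, by county, will vary due to the targeted sampling of metro counties (25 practices per county"), against "more rural counties (one to five practices per county"). The section then states that "a jackknife estimate of the variance will be used to maintain the size of the test". It sets aside the small-sample limits of GEE because there are 263 practices and 11 time points.
- **Analytic plan, region.** Region enters as four indicators: "indicator for each quadrant, with the combined Tulsa and Oklahoma City metro areas serving as the reference group". The interaction with support is judged by a Type III Wald statistic, with region described as having five degrees of freedom. As an alternative, "a dichotomous region variable indicating metro versus non-metro locations will be considered".
- **Analytic plan, alpha.** "A 2-sided 0.05 alpha level will be used to define statistical significance".
- **Sampling methods.** The sectors are "4 quadrants of the state plus 2 metropolitan areas of Oklahoma and Tulsa counties". The target was 50 practices per quadrant, and "25 practices were sampled per metro area". In all there are 75 counties or paired county units.

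**The concern.** A jackknife over clusters needs enough clusters in each group being compared. Seventy-five county units are ample for the overall support effect. They are not ample for a contrast in which one side is two counties, because the variance on that side then rests on a single between-county difference. The article's reassurance about 263 practices does not reach this case.

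At stake is the claim of effect modification by region, and in particular whether support works differently in metro and rural practice. Under the plan's rule a significant interaction marks a modifier. If the test rejects two to three times as often as 0.05 allows, a spurious urban-rural difference could be reported with the plan's own assurance that its size was protected.

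**Working it through.** **Inputs from the article.** Two metro counties with 25 practices each (50 in all); 50 practices in each of four quadrants (200 in all); 75 county units, hence 75 - 2 = 73 non-metro units, about 18 per quadrant; 1-5 practices per rural county; 11 time points; four waves randomised by practice within 20 sub-regions; two-sided alpha 0.05.

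**Assumptions not in the article.** Variance components, wave start periods, patients per practice and quarter, any county-level variation in effect or trend, and the large-sample reference for the Wald statistic.

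**Step 1: the two-county level alone.** Let the two county estimates differ by d.

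- Deleting either county moves the metro mean by d/2, so the jackknife variance is (74/75) × 2 × (d/2)², about d²/2.
- The unbiased variance of the mean is s²/2 with s² = d²/2, that is d²/4, on 1 df.
- The jackknife is therefore about twice the unbiased estimate. A cut-off of 1.96 becomes 1.96 × √2 = 2.77 on a t with 1 df.
- P(|t₁| > 2.77) = 1 - (2/π) arctan(2.77) = 0.22.

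**Step 2: dilution by the non-metro side.** With variance proportional to 1/practices, metro carries f = (1/50) / (1/50 + 1/200) = 0.80 of the variance of metro versus non-metro. If the non-metro part is treated as known, the rejection rate is E[2Φ(-1.96 √(2fW + 1 - f))], with W chi-square on 1 df:

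| f | rejection rate |
|---|---|
| 0.80 | 0.12 |
| 0.90 | 0.16 |
| 1.00 | 0.22 |

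If the support effect itself varies between counties, f moves towards (1/2) / (1/2 + 1/73) = 0.97, so the rate rises.

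**Step 3: simulation under a true null.** Linear GEE with period, region, support and support-by-region terms; delete-one-county jackknife with factor (n-1)/n; 2,000 data sets per scenario (Monte Carlo SE about 0.5-0.9 points). Scenarios varied outcome type (continuous, or binary with 30 or 100 patients per practice and period), working correlation, wave timing, and variation of effect or trend by county.

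The stated 0.05 was checked first, on the main support effect. It is reproduced there, at 4.1-6.5%.

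| Test, county jackknife | Rejection rate |
|---|---|
| Main support effect | 4.1-6.5% |
| Region by support, chi-square(4), no county-level variation | 11.8-12.6% |
| Same, county-by-period variation | 13.9% |
| Same, county-by-support variation | 14.8-18.3% |
| Same statistic, F(4, n-5) | 10.7-16.0% |
| Same statistic, chi-square(5) | 8.3-13.4% |
| Metro versus non-metro, 1 df | 10.7-19.0% |
| Four quadrants only, 3 df, chi-square | 6.2-7.4% |

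A separate simulation used two-way fixed effects on practice-quarter rates, 213 non-metro practices and about 1,000 trials per scenario. It gave 11-17% for the region test, 12-17% for metro versus non-metro, and 4-8% for quadrants only with an F reference.

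**Step 4: isolating the cause.** Treating the same 50 metro practices as 18 clusters instead of 2, with no county effects, brings the region test down to about 7%. The overall Wald statistic is the same whichever level is the reference, so the coding is not the cause.

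**Step 5: the stated df.** Five levels coded by four indicators give 4 df. The 5% cut-offs are 9.49 for chi-square(4) and 11.07 for chi-square(5). A true 4-df statistic exceeds 11.07 with probability 0.026. The df error therefore partly masks the inflation, which is why the chi-square(5) row is lower.

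**The case against.** **The deletion unit is not fixed.** The article cites county sizes as the reason for the jackknife but does not say what is deleted. The sentence before gives the clustering as practice units within practices within sub-regions, and the practice is the randomised unit. Deleting by practice gives 5.3-6.3% when effects and trends do not vary by county. This stands, and it makes the finding conditional. It is not a full escape: where effects or trends do vary by county, deleting by practice rejected between 14% and 55%, depending on the variation assumed. Deleting by sub-region gave 16-31%. County remains the best-supported reading, since the jackknife sentence is about counties and the patient-level and event models also cluster by county.

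**Counties are exhausted, not sampled.** The two counties are the whole metro level, so county can be treated as a fixed stratum. This is a legitimate choice, but the plan has to state it along with its assumption.

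**The reference distribution is not given.** An unseen analysis plan might supply one. However, an F with n-5 denominator df still leaves 10.7-16.0%, and the article explicitly dismisses small-sample concerns.

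**Region is only a modifier, and the metro dichotomy is optional.** This is correct and limits the importance of the point.

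**The counts are targets.** The 25 practices per metro county come from a design of 250; the text gives no county counts for the 263 recruited. The two-county structure does not depend on these counts, though the exact rates do.

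**Conclusion.** The point holds in conditional form. With counties deleted and a large-sample reference, the region-by-support test has a true size of about 11-18% on 4 df, or about 8-14% on the stated 5 df, and metro versus non-metro about 11-19%. These are ranges because the variance components are assumed. The property claimed for the jackknife fails for any test that involves the metro level.

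A reader might infer more than the documents support:

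- *That the trial's main result is at risk.* It is not; the main support effect keeps its size at about 4-6.5%.
- *That one inflated error rate follows from the plan as written.* It does not; the deletion unit and reference distribution are not fully stated, and the five df lower the rate.
- *That choosing metro as reference causes the problem.* It does not; the cause is a level with two clusters.
- *That metro must be left out of all inference.* That goes further than needed, because inference limited to these two counties is possible under a stated assumption.

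**What to change.** In the Analytic plan:

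1. Restrict the statement that the jackknife maintains size to the main support effect.
2. State the unit that the jackknife deletes.
3. Correct the region factor to 4 df, to match its four indicators.
4. For any contrast involving metro, choose one of two routes:
   - (a) Limit inference to these two counties and use the practice, the randomised unit, as the variance unit. State the assumption that effects and trends do not vary by county.
   - (b) Keep county clusters and report the metro difference as an estimate with a Satterthwaite-df interval. Make the formal region test a comparison among the four quadrants on 3 df with an F reference. In simulation this test rejected 4-8%, so it is close to nominal but not exact.

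The change is to analysis wording only; data, recruitment and randomisation stay as they are. Under (a) the metro-versus-rural claim is narrower and depends on the stated assumption. Under (b) there is no significance claim for metro against rural.

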#### Data sources

The H2O master dataset will include both primary and secondary data sources. The aforementioned surveys will be compiled to include variables describing organizational contexts and outputs. These data are collected by PFs during visits to practices at three time points: (1) baseline, (2) at the end of the implementation of support strategy, and (3) 6 months post-implementation. Secondary data on performance (e.g., ABCS) and patient-oriented outcomes (e.g., hospitalization, length of stay) is extracted from the EHRs and the HIE. Practice performance, i.e., the number of patients who achieved and provider performance on these measures, will be calculated for each practice (Table 2).

**Table 2 Tab2:** Outcome measures from HIE and/or EHR data

Measure (Source)	Numerator	Denominator*	Exclusion	Data Source
Aspirin (PQRS 204/NQF 0068)	Patients in denominator with documented use of aspirin or other antithrombotic	Patients 18+ years of age with Ischemic Vascular Disease diagnosis, or hospital discharge for acute myocardial infarction, coronary artery bypass graft, or percutaneous coronary interventions	On another anticoagulant, GI bleeding history, aspirin allergy	Health Information Exchange (HIE)
Blood Pressure Management 1 (PQRS 236/NQF 0018)	Patients in denominator whose blood pressure was adequately controlled (< 140/90)	Patients aged 18 through 85 years with a diagnosis of hypertension	End stage renal disease, dialysis, renal transplant, or diagnosis of pregnancy	HIE
Blood Pressure Management 2	Patients in denominator whose blood pressure was adequately controlled (age 18–59 and/or people with diabetes or chronic kidney disease < 140/90; age 60–85 < 150/90)	Patients aged 18 through 85 with a diagnosis of hypertension	Lacking a DM or CKD diagnosis	HIE
Cholesterol Management 1 (PQRS 316)	Patients in the denominator whose risk-stratified fasting LDL is at or below the recommended LDL goal	Patients aged 20 through 79 years of age who had a fasting LDL performed		HIE and chart audits
Cholesterol Management 2	Patients in the denominator who were prescribed the recommended dose of statin based on risk status	Patients aged 20 through 79 years of age who had a fasting LDL performed		HIE and chart audits

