
Logistic regression models will be fit to estimate the effect of the implementation support strategy on the log odds of attaining an ABCS criterion for a given patient. The outcome variable will be a Yes/No indication of attaining an ABCS criterion measured at a patient level. Individual-level data will be analyzed where the nested clustering of patients within practice units, nested within practices and counties will be accounted for using a structured working correlation structure [44].

Poisson regression models, with a log link, will be used to estimate the effect of the implementation support strategy on the incidence rate of patient outcomes, (ED visits, preventable hospitalizations, heart attacks, strokes, GI bleeds, deaths, etc.), where practice unit data are summarized for each 3-month time period. The outcome will be the number of patient events reported among the active adult patients in a practice unit and the offset will be the total number of patient-months of time at risk during the 3-month time period for the practice unit. GEE will be used to account for the correlation among nested practice units within practices within counties and modifying factors will be investigated.(2)Role of internal and external contextual factors and intervention characteristics on the uptake of the implementation support strategy and on practice performance and outcomes.

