General regression modeling strategies described by Baron and Kenny [45] will be used to investigate modifying and mediating factors, as presented in the Logic Model, controlling for clustering. In brief, factors that modify the effect of the implementation support strategy will be indicated by significant interaction terms in the regression model. For example, organizational contextual factor scores will be investigated as modifying factors to determine if there is evidence that the effect of the implementation support strategy is greater among those practice units that have higher scores on the contextual factors. Mediating variables will be investigated by fitting a series of four regression models. First, the effect of the implementation support strategy on the health outcome measure will be estimated. Second, the association between the implementation support strategy (independent factor) and the potential mediating factor (outcome) will be estimated. Third, the association between the mediating factor (independent factor) and the health outcome variable will be estimated. Finally, the model will be refit to include the implementation support strategy and mediating term as independent factors with the health outcome measure modeled as the outcome variable. A change in the implementation support strategy coefficient, indicating a shift towards no effect on the outcome, with adjustment for the mediating factor will provide evidence of a mediating association.

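### The mediation steps can point to mediation for a mediator that does nothing: step 3 omits the support term, and step 4 does not separate within-practice change from stable practice level

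*Protocol article*

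**What the plan says.** The mediation method is in the protocol article, Analytic plan, under the second analytic goal. The four regressions are outcome on support, mediator on support, outcome on mediator, and outcome on both.

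- Step 3: "Third, the association between the mediating factor (independent factor) and the health outcome variable will be estimated". No support term is named.
- Step 4: "the model will be refit to include the implementation support strategy and mediating term as independent factors". Here the support term is named, so its absence from step 3 reads as intended.
- Decision rule: "A change in the implementation support strategy coefficient, indicating a shift towards no effect on the outcome, with adjustment for the mediating factor" is taken as evidence of mediation. No minimum shift, test or interval is given.
- Protection named for these models: they are fitted "as presented in the Logic Model, controlling for clustering". The text says nothing about centring, baseline adjustment or a within/between split of the mediator.

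Candidate mediators include the practice survey scores (change process capability and Adaptive Reserve, under Surveys). Data sources says of the survey data: "These data are collected by PFs during visits to practices at three time points". These are baseline, the end of support, and six months after it, so one reading falls before support and two after.

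**The concern.** The two steps have different weaknesses.

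**Step 3.** Support is a common cause. If it raises both the mediator score and the outcome, the two are associated with no path between them. A significant step 3 then says little beyond the fact that support works.

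**Step 4.** The start of support is randomized, but a practice's score is not. Change capacity and Adaptive Reserve describe lasting features of a practice, and the Logic model section has inputs, outputs and external factors all bearing on outcomes. Practices with lastingly high scores may therefore also have lastingly good ABCS levels. Clustering control through GEE corrects standard errors but does not remove this between-practice association from the mediator coefficient. Because support raises the score, the mediator then takes credit for part of the support effect, and the support coefficient moves towards no effect. That is the pattern the plan reads as mediation.

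At stake is the explanation of how support works, which is the purpose of the second analytic goal. A formal test of the indirect effect alone would not cure it, because the mediator coefficient going into that test would still be biased.

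**Working it through.** The article states no error rate or power for the mediation analysis, so there is no figure of its own to reproduce. The powers in Table 3 concern the total support effect.

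**Inputs from the article.** "263 practices will serve as the unit of randomization and 11 time points will be utilized in the design"; three survey times; two-sided alpha 0.05; within-practice correlation 0.10 or less (0.10 used); effects in Table 3 (aspirin 60% to 70%, blood pressure 65% to 70%). The working correlation is described as structured ("nested within practices and counties will be accounted for using a structured working correlation structure"), with no form given, so independence and exchangeable were both tried.

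**Assumptions not in the article.** 50 patients per practice and period; support raises the score by a = 0.5 SD; half of the score variance is stable between practices; correlation ρ between stable score and stable outcome level of 0, 0.3 or 0.5. The true mediator effect is set to 0.

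**Model.** Score M = T + aX + e. Outcome on the logit scale = U + cX. Corr(T, U) = ρ. M has no effect on the outcome.

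**Step 3 at ρ = 0.** The slope of outcome on M is a·c·Var(X) / Var(M). With support coded 0, 1, 1, Var(X) = 2/3 × 1/3 = 0.222. For aspirin, c = ln(0.7/0.3) − ln(0.6/0.4) = 0.847 − 0.405 = 0.442. The slope is 0.5 × 0.442 × 0.222 / (1 + 0.25 × 0.222) = 0.0491 / 1.056 = 0.047, not 0. Logistic GEE simulation (independence) gave 0.042.

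**Step 4, independence.** The mediator coefficient is b = ρ·sd(T)·sd(U) / Var(M given X), and the share of the support effect lost is a·b/c.

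- sd(U) = √(0.10/0.90 × π²/3) = 0.605; sd(T) = √0.5 = 0.707; Var(M given X) = 1.
- ρ = 0.3: b = 0.3 × 0.707 × 0.605 = 0.128, and a·b = 0.064.
- ρ = 0.5: b = 0.214, and a·b = 0.107.
- Aspirin: 0.064/0.442 = 14.5% and 0.107/0.442 = 24%.
- Blood pressure: c = 0.847 − ln(0.65/0.35) = 0.228, so 28% and 47%. The same spurious shift is a larger share of a smaller effect.

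An exchangeable structure gives between-practice contrasts less weight, so the loss is smaller.

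**Simulation, aspirin effect, three-survey layout, 200 data sets per setting, null mediator.**

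| Setting | Step 3 significant | Step 4 mediator significant | Support shifts to null | Mean attenuation |
|---|---|---|---|---|
| ρ=0, independence | 26% | 4.5% | 52% | about 0 |
| ρ=0, exchangeable | 100% | 8.5% | 54% | about 0 |
| ρ=0.3, independence | 100% | 98% | 100% | 14% |
| ρ=0.3, exchangeable | 100% | 37% | 93% | 3% |
| ρ=0.5, independence | 100% | 100% | 100% | 23% |
| ρ=0.5, exchangeable | 100% | 76% | 99% | 5% |

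The step 4 mediator column is also what step 3 would give with support added. At ρ = 0 that addition cures step 3 (26% to 4.5%, 100% to 8.5%). At ρ = 0.3 to 0.5 it does not.

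For scale, a real mediator effect of 0.3 log-odds per SD gave 24% attenuation. Under independence, a null mediator at ρ = 0.5 looks the same.

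**Eleven-period, four-wave check (60 data sets, ρ = 0.5).** Attenuation was 25% with a shift in 100% of runs (independence), and 1% with a shift in 83% (exchangeable). Taken with a further set of runs, the ranges at ρ = 0.3 to 0.5 are about 14-45% (independence) and 1-13% (exchangeable).

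**With the mediator split into practice mean and within-practice deviation.** At ρ = 0.3 to 0.5 in the three-survey layout, the within-practice term is significant in 2-7% of runs and attenuation is about 0 (−0.4% to −1.5%). In the eleven-period layout under independence, 16% attenuation remained. The practice mean carries each practice's own support exposure, and it was in the step 4 model but not in step 1.

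**The case against.** Several objections have weight.

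- **The article does not say that the scores are raw.** It is silent on how the mediator is parameterised, it introduces the method as a summary, and a fuller plan may settle the point. That stands as to wording. But the article does fix the four models and the decision rule, and the only safeguard it names does not remove the bias.
- **A within/between phrase appears elsewhere in the Analytic plan** ("based on a within-cluster and between-cluster analysis"). It concerns the effect of support on the capacity-to-change score as an outcome, not the score as a predictor, so it does not answer the point.
- **Step 3 is not the decision rule.** Correct. The rule compares steps 1 and 4, and nothing makes step 3 a gate. The omission makes step 3 uninformative, not decisive.
- **The step 4 bias needs an assumed practice-level correlation.** Correct. At zero correlation step 4 is unbiased.
- **The largest figures come from independence working correlation**, which is not the natural reading of a structured one. Fair. Under exchangeable correlation the attenuation is small. The rule sets no minimum, however, so even a small systematic shift satisfies it.
- **Part of the shift count comes from that missing threshold.** With a null, unconfounded mediator the shift is towards zero in 52-54% of runs. The confounding accounts for the rise from there to 83-100%.

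A reader might infer that mediation would be confirmed almost regardless of the truth. The documents do not support this: the false signal in step 4 depends on a correlation they do not give, and its size on a working correlation they do not specify.

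**Conclusion.** The point holds in a limited form. Step 3 as written cannot distinguish a working mediator from one that support merely moves alongside the outcome. Step 4 as described, with no separation of stable practice level from within-practice change, is biased if the two levels are correlated across practices. With an assumed correlation of 0.3 to 0.5 and a null mediator, the support coefficient shifts towards no effect in 83-100% of runs, by about 1-13% (exchangeable) or 14-45% (independence). With no such correlation, mean attenuation is about zero.

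These sizes also rest on the assumed score shift of 0.5 SD, the share of stable score variance and the number of patients per practice, none of which the article gives. The direction of the bias was the same in every confounded setting tried.

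It would be wrong to read this as a threat to the main result. The estimate and test of the support effect on ABCS are unaffected. What is at risk is the claim about mechanism.

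**What to change.** In the mediation paragraph of the Analytic plan:

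1. Include support in step 3, or drop step 3 and read the mediator-outcome path from step 4.
2. Enter each mediator as within-practice deviation plus practice mean, or use practice fixed effects. Put the same practice-level terms in the step 1 and step 4 models whose support coefficients are compared. Otherwise the practice mean can itself move the coefficient, as in the 16% case above.
3. Adjust for calendar time in a form the data can identify. With one survey before support and two after, centring alone does not separate support from time.
4. Base the mediation conclusion on the within-practice path, with a cluster-level interval for the indirect effect in place of the direction of the shift. Report the between-practice term as descriptive.

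The cost is analysis wording only, since the three surveys are already planned. The interval for the mediator path will be wider because between-practice differences are no longer used. Confounding that varies over time within a practice remains, for example from staff turnover or a new EHR, both of which the article names as reasons for drop-out. It should be stated as a limitation.

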#### Analytic plan

The evaluation plan has 2 analytic goals: (1) determine the impact of the implementation support strategy on the practice’s capacity to change, performance indicators and patient outcomes; and (2) assess the role of internal and external contextual factors and intervention characteristics on the uptake of the implementation support strategy and on practice performance and outcomes.Impact of the implementation support strategy on the practice’s capacity to change, performance indicators and patient outcomes

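### The mediation criterion is any shift of the support coefficient towards no effect, with no test or interval for the indirect effect; read literally, a factor that mediates nothing often meets it.

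*Protocol article*

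**What the plan says.** The mediation paragraph closes the Analytic plan in the Protocol article. It names its source, "General regression modeling strategies described by Baron and Kenny [45] will be used to investigate modifying and mediating factors", and then summarises the procedure: "Mediating variables will be investigated by fitting a series of four regression models".

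- Model 1: "First, the effect of the implementation support strategy on the health outcome measure will be estimated".
- Model 2: "the association between the implementation support strategy (independent factor) and the potential mediating factor (outcome) will be estimated".
- Model 3: "Third, the association between the mediating factor (independent factor) and the health outcome variable will be estimated". Support is not mentioned as a term in this model.
- Model 4: support and the mediator enter together, with the health outcome as the response.

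The only criterion given is the comparison of models 1 and 4: a change in the support coefficient "indicating a shift towards no effect on the outcome, with adjustment for the mediating factor will provide evidence of a mediating association". The paragraph treats modifiers differently, since those are to be identified by statistically significant interaction terms. The two-sided 0.05 level is stated earlier, under the first analytic goal, and is not tied to the mediation steps.

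**The concern.** The criterion is the direction of change in one coefficient between two fitted models. Chance alone moves that coefficient in one direction or the other, and the text does not say how large a move counts or how its uncertainty is judged. The first three models are to be estimated, but no result from them is required before the comparison is interpreted. Model 3 is also a weak safeguard if it is used as one. When support affects both the mediator and the outcome, the two are associated even if the mediator does nothing.

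The mediation analysis is where the plan would say how the support works. It belongs to the second of two analytic goals, and the article's abstract says that the lessons learned will guide later implementation strategies. Factors wrongly named as mechanisms would misdirect that work. No ABCS effect estimate under the first goal depends on it.

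**Working it through.** The article gives no error rate, power or sample size for mediation, so there is no figure to reproduce. The check is algebra, then simulation.

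**Algebra.** Let c be the support coefficient in model 1, c′ the support coefficient in model 4, a the support-to-mediator coefficient in model 2, and b the mediator coefficient in model 4. In linear least squares with the same covariates throughout,

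c − c′ = a × b, exactly.

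If c is clearly non-zero and a × b is small beside it, the coefficient moves towards zero whenever a × b has the sign of c. If the mediator has no effect on the outcome, the estimate of b is symmetric about zero, so this happens with probability 1/2. The same holds if support does not move the mediator, because the estimate of a is then symmetric about zero.

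**Inputs from the article.** 263 practices, 11 time points and four waves; logistic models for the ABCS criteria; the aspirin row of Table 3, 60% to 70%. The log odds ratio is ln(0.70/0.30) − ln(0.60/0.40) = 0.847 − 0.405 = 0.442.

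**Assumptions, not in the article.** One wave starts per period; the effect is a step; 50 patients per practice-period; linear support effect 0.3; a of 0 or ±0.5; b of 0, 0.3 or 1; mediator SDs 0.6 between practices and 0.8 residual. Models include period effects, with practice-clustered standard errors. There were 1,000 linear and 500 logistic runs per scenario.

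**Share of runs in which a factor that mediates nothing is flagged:**

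| Scenario | Linear, any shift | Linear, steps 1–3 also significant | Logistic, any shift | Logistic, steps 1–3 also significant |
|---|---|---|---|---|
| a=0, b=0 | 48.1% | 0.1% | 51.0% | 0.0% |
| a=0.5, b=0 | 48.0% | 3.9% | 50.0% | 9.8% |
| a=−0.5, b=0 | 48.5% | 3.4% | 50.8% | 8.4% |
| a=0, b=0.3 | 49.1% | 3.2% | 38.2% | 2.0% |
| a=0, b=1 | 50.9% | 2.1% | 17.8% | 1.8% |

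With no support effect at all (linear, a=b=0) the any-shift rate was 51.4%. The lower logistic figures in the last two rows arise because adjusting for a predictor of the outcome moves a log odds ratio away from zero.

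A cruder logistic layout (before and after support, 40 patients per practice, 65% to 70%, 600 runs) gave 52% for an inert mediator that support moves, 48% for a factor unrelated to both, and 42% for a prognostic factor that support does not move. The simulation error at one half is √(0.5 × 0.5/600) = 2.0 points, so the first two agree with 50%.

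**What happens to the gate when support moves the mediator more.** In linear runs with an inert mediator, support effects on the outcome of 0.3 to 0.5 SD, and steps 1–3 all required at 0.05, the false-mediator rate was 4–11% when support moves the mediator by 0.5 SD, 14–28% at 1.0 SD, 18–47% at 1.5 SD and 31–49% at 2.0 SD. The levels depend on the assumed variances: a repeat with SDs of 0.6 and 0.8 for both mediator and outcome showed the same rise at somewhat lower levels. The direction is the dependable part. Model 3 becomes significant through support, and the sign of the shift is then left to chance.

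**With the indirect effect tested.** In the scenarios of the table, joint significance of a and b gave 0.0–6.4% and the Sobel test 0.0–4.6%. A true mediator (a=0.5, b=0.3) was detected in 100% of runs. The bootstrap interval proposed below was not itself simulated.

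**With mediator-outcome confounding (a=0.5, b=0).** The any-shift rate was 99.8% (linear) and 100% (logistic), and the indirect-effect tests flagged 100% and 99.8%. Testing does not cure confounding.

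**The case against.** The article is a condensed account. It marks the mediation summary as brief and cites a published multi-step method, so a reader may fairly take the first three models as conditions that must be met and expect the test in a fuller plan. It also says only that a shift provides evidence, which is softer than declaring a mediator. If steps 1–3 are conditions, the table shows 0–3.9% (linear) and 0–9.8% (logistic), and if the mediator must also be significant in model 4, 0–3.2%. Model 4 already supplies the support-adjusted mediator coefficient, so the ingredients for an indirect effect are planned.

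Much of this stands. It limits the size of the problem and makes the repair easy. It does not remove the point, because the article does more than omit a detail: it states a criterion, and that criterion is a bare shift. It asks for significance where modifiers are concerned and not here. The gate that a reader might supply also weakens for the factors that support moves most.

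Two stronger readings are tempting and not supported. One is that any non-mediator is flagged about half the time. That holds for linear models and for inert mediators in logistic models, read literally, but not for prognostic factors in logistic models or under a gated reading. The other is that the behaviour of log odds ratios under adjustment adds to the false positives. It pushes the coefficient away from zero and so lowers them, although it still shows that the shift reflects more than mediation.

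The second goal is also wider than mediation. It is to "assess the role of internal and external contextual factors and intervention characteristics on the uptake of the implementation support strategy" and on performance and outcomes, and the article's worked example concerns modifiers.

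**Conclusion.** The concern holds in a limited form. The Analytic plan takes a shift towards no effect as evidence of mediation, with no test or interval for the indirect effect and no statement that the earlier steps are conditions. Read literally and without mediator-outcome confounding, the false-mediator rate is about 50% in linear models and about 18–51% across the main logistic scenarios. With steps 1–3 as gates at 0.05 it is about 0–10% for modest support-to-mediator effects, and higher for strong ones.

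The linear 50% follows from algebra and depends little on the inputs. The logistic and gated figures depend on the assumed path sizes, variances and roll-out. The log-link models for event rates were not simulated.

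**What to change.** Replace the last sentence of the mediation paragraph so that evidence of mediation rests on an estimate of the indirect effect:

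- Take support-to-mediator from model 2, and mediator-to-outcome from model 4 with support, calendar period and measured baseline practice characteristics included.
- Use the product of coefficients for linear models and the risk-difference scale for logistic outcomes, where a comparison of log odds ratios is not a clean measure of mediation.
- Give a 95% interval from a bootstrap that resamples whole practices, and speak of evidence of mediation only when it excludes zero.
- Say that models 1 and 3 are descriptive and not conditions.
- State that the mediator is not randomised, so unmeasured mediator-outcome confounding remains a limitation that the interval does not remove.

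This needs no new data. It costs a few lines of text and some computing time, and fewer factors will be called mediators.
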